##### Non-theory based implementation arm

In the non-theory based arm, participants will be presented with a table of intuitively derived barriers and intuitively derived solutions.

Participants will be provided with a feasibility/impact matrix for each proposed strategy in both arms, and asked their opinions on the anticipated effort needed, feasibility and impact, guided by the APEASE criteria [38]. From this, the core intervention components will be refined.

#### Phase 6 - support staff to implement interventions

Intervention strategies generated in phase 5 will be implemented using general implementation science principles (i.e. the need for management support and commitment among target group members, use of boundary spanners, flexibility driven by local context, incorporation into established structures) [16]. With a template provided by the research team, Implementation Leads will create a report that will outline findings from phase 1–5, the intervention package and a plan for implementation. This will be submitted to senior management from departments affected by any proposed intervention strategies (e.g. CRC surgery, pathology and FCCs), and may require revision based on management feedback. Once management approves the proposed implementation plan, intervention strategies will then be presented to relevant forums (e.g. MDT meetings, pathology team meetings) to gain feedback that will allow the development of a broader structure to disseminate findings. The Implementation Lead will then work collaboratively with the Implementation Team to implement the intervention package over a 6-month period.

#### Phase 7 - evaluate intervention and assess practice and culture change

Following the 6-month intervention implementation period, LS patient pathway stakeholders from both arms will be invited to complete a second IPSBQ to assess any changes in perceived barriers to improving LS referral and diagnosis, as part of the simultaneous process evaluation. In addition, post-intervention clinical data will be extracted and compared to baseline clinical data to assess the impact of the intervention on clinical practice change, via assessment of the proportion of patients with CRC with risk-appropriate completion of the LS referral pathway.

### Analysis plan

#### Sample size and statistical power

The qualitative and descriptive outcomes (including the LS referral process maps, the descriptive baseline clinical data, the IPSBQ questionnaire results) are not amenable to sample size calculations. While it would be ideal to carry out a power calculation for the proportion of patients with risk-appropriate completion of the LS referral pathway, it is not possible in this situation due to the lack of exploratory trials in this area, including paucity of information on baseline outcomes, the number of patients per hospital and the intra-cluster coefficient (ICC) for outcomes in this trial. The power calculation will therefore be carried out once the baseline information is obtained. We also acknowledge that despite random allocation of the eight clusters, the characteristics may not be balanced between the two arms of the trial, representing a limitation of this trial.

#### Analysis of baseline clinical data

For each hospital network, the baseline clinical data extracted in phase 1 will be analysed for concordance with the hospital-specific LS referral pathway. Patients who transition through each step - in adherence to the pathway map - will be leading to the identification of bottlenecks. In the event that 100% adherence is demonstrated at baseline, investigators from the relevant site will be offered the option of continuing or withdrawing from the trial.

#### Assessing perceived barriers via questionnaire

Results from the IPSBQ will be analysed using descriptive statistics. Inter-item correlation will be tested to assess the internal consistency of each IPSBQ subscale (optimal range = 0.15–0.50). Pre-post questionnaire results from both trial arms will be used to assess changes in barriers as part of the aforementioned process evaluation.

#### Theory-based focus group data analysis to design intervention strategies

Stage 1: in line with previous approaches [16], focus group data will be thematically analysed using a deductive approach, with coding according to the TDF domains. The key barrier domains emerging from the focus groups will be cross referenced with those identified by the IPSBQ, and discrepancies noted.

Stage 2: analysis of the top 3–4 barrier domains will identify overlap with existing theories of behaviour change. These theories will be reviewed to identify experimental data that has demonstrated the mechanistic effect of specific behaviour change strategies for eliciting behaviour change. This review will be used to identify categories of BCTs that may be effective [44, 45]. These techniques will be operationalised into context-specific intervention strategies to address the key barriers to generate an initial intervention package, which will be reviewed and refined in collaboration with each Implementation Lead.

#### Non-theorybased focus group data analysis to design intervention strategies

Stage 1: inductive analysis will be applied to identify key intuitively derived barriers reported in the focus groups.

Stage 2: context-specific intervention strategies will be identified to address the key barriers to generate an initial intervention package, which will be reviewed and refined in collaboration with each Implementation Lead.

#### Focus group data analysis to refine the intervention package

Deductive analysis on the second set of focus group data will be applied in both trial arms, based on the APEASE [38] criteria, to assess the perceptions of the feasibility and impact of each proposed intervention strategy. From this, the core intervention components will be refined.

#### Assessing clinical practice change

The analysis of each dichotomous study outcome will be conducted at the individual patient level, using generalised estimating equation (GEE) adjustment for the clustering of patients within hospital networks. We will estimate the adjusted relative proportion (RR) of patients with the outcome using a generalised linear regression model with Poisson distribution, log link and robust standard errors. The exposure variable will be the implementation intervention status of the respective hospital network at the time of the patient’s CRC resection (pre or post implementation-intervention). We will carry out a two-sided test for each outcome, with the significance threshold defined using the Bonferroni correction for the number of outcomes tested. Missing testing and/or referral data will be treated as tests not carried out, or referral not completed, respectively. As covariates, we will consider time period (3-month intervals), time since implementation of intervention strategies (3-month intervals), patient age at operation, sex and cancer stage. The Quasi-Akaike information criterion will be used to select which covariates to include in the final model. To account for non-independence of within-hospital outcomes, all GEE analyses will be carried out with exchangeable working correlation structures. We will carry out sensitivity leave-one-out analyses by individually excluding hospital networks that accounted for more than 20% of the total patient numbers. If private patient status can be reliably obtained in at least six of eight trial sites, a supplementary analysis will be performed using private patient status as an additional covariate.

We note previous studies have found that a small number of clusters can lead to inflated type I error rates, and so-called small-sample corrections have been proposed to address this. However, these small-sample corrections were found to be too conservative for eight clusters [46]. Consequently, we will carry out a supplementary analysis using small-sample correction only for those outcomes that are robustly significantly associated with the implementation intervention status.

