## Abstract

**Background:**

Lynch syndrome (LS) is an inherited, cancer predisposition syndrome associated with an increased risk of colorectal, endometrial and other cancer types. Identifying individuals with LS allows access to cancer risk management strategies proven to reduce cancer incidence and improve survival. However, LS is underdiagnosed and genetic referral rates are poor. Improving LS referral is complex, and requires multisystem behaviour change. Although barriers have been identified, evidence-based strategies to facilitate behaviour change are lacking. The aim of this study is to compare the effectiveness of a theory-based implementation approach against a non-theory based approach for improving detection of LS amongst Australian patients with colorectal cancer (CRC).

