**Fig. 1 Fig1:**
[figure not shown]
Consolidated Standards of Reporting Trials statement extension for social and psychological interventions (CONSORT-SPI) flow diagram. Diagram of participant (hospital networks) recruitment. *Numbers to be incorporated as trial progresses

A parallel, cluster randomised trial will be used to test for differences between a theory-based implementation approach (TDFI) and a non-theory based implementation approach to improving LS referral practices in eight large Australian hospital networks across three states [New South Wales (n=4), Victoria (n=2), and Western Australia (n=2)]. As sharing of staff and resources in networked hospitals is likely to lead to correlations between outcomes, each hospital network will comprise a separate cluster in this trial (i.e. eight clusters in total). Hospital networks will be randomly allocated to the theory arm or non-theory arm using a computer-generated random sequence. To account for differences in region-specific LS detection pathways, the randomisation will be stratified by participating states, with the same number of networks from each state allocated to theory and non-theory arms (a 1:1 allocation ratio). A theory-based, mixed methods process evaluation will be conducted alongside the trial to investigate intervention fidelity, potential mechanisms of impact, mediators and contextual moderators, for both approaches [24, 36].

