## Discussion

The implementation of a systematic approach to LS identification and referral is complicated, and requires behavioural change amongst a multidisciplinary team of healthcare professionals working within a complex and unpredictable system. Results from the pilot study highlighted a number of theoretical and practical issues related to using a theory-based implementation approach to addressing the LS referral problem in this context - a possible explanation for the lack of improvement in referral overall [30]. By engaging someone from within the system to lead the implementation approach we seek to overcome these issues, enabling us to determine the extent to which the use of theory-based implementation approaches are (1) feasible in this setting and (2) more effective than approaches reliant on the intuition and tacit knowledge of healthcare professionals.

In addition to addressing a known clinical problem, this will be the first study to compare the effects of two implementation approaches, distinguished only by the use of theory to determine psychosocial barriers and intervention development to translate evidence into practice in complex healthcare systems. By analysing clinical practice data pre-post intervention, we will determine the more effective approach for increasing the proportion of patients with CRC with risk-appropriate completion of the LS referral and testing pathway, and the difference in the types of strategies generated through theory-driven and intuitive approaches taken to achieve this. This will also build on the work of Brennan and colleagues [11] to enhance understanding of LS referral and diagnostic practices in Australia.

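### The only outcome model compares pre with post implementation and omits the randomised arm, so as written it does not estimate theory versus non-theory

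*Protocol article*

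**What the plan says.** The question is comparative throughout. The abstract's Background sets out to "compare the effectiveness of a theory-based implementation approach against a non-theory based approach for improving detection of LS". The Design section says: "A parallel, cluster randomised trial will be used to test for differences between a theory-based implementation approach (TDFI) and a non-theory based implementation approach". Networks are allocated 1:1 within state: "New South Wales (n=4), Victoria (n=2), and Western Australia (n=2"). The Discussion promises: "By analysing clinical practice data pre-post intervention, we will determine the more effective approach".

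The analysis is given under Assessing clinical practice change. It is a patient-level Poisson GEE with log link, robust standard errors and exchangeable correlation within network. On the exposure it says: "The exposure variable will be the implementation intervention status of the respective hospital network", with status taken at the patient's "CRC resection (pre or post implementation-intervention"). The candidate covariates are calendar period, time since implementation, age, sex and stage, chosen by quasi-AIC. Private patient status may be added in a supplementary analysis. The small-sample correction is reserved for outcomes significantly associated with the same pre/post status.

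Post-implementation outcomes defines the primary outcome as a change in a proportion and names no contrast between arms. Phase 7 describes post-intervention data compared with baseline.

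**The concern.** Both arms go through all seven phases and put an intervention package in place; they differ only in phases 4 and 5. Every network therefore moves from pre to post. A coefficient on pre/post status measures how far completion changed across all eight networks. It does not measure whether the change was larger in one arm.

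Followed as written, the plan would yield a before-after RR that randomisation does not protect. A significant result could be reported from a trial labelled randomised and still say nothing about theory. The Discussion's claim to identify the better approach would rest on no specified estimate or test.

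**Working it through.** The article states no sample size, power or numerical alpha, so there is no figure to reproduce. The check is whether the specified coefficient responds to an arm difference.

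**Inputs.** From the article: eight networks, four per arm, and the model described above. Assumed, because the article does not give them: 300 pre and 110 post patients per network, and 40% baseline completion in every network. Post-implementation completion was varied by arm with its average held at 60%.

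**Specified model (pre/post only).** With equal baselines and equal arm sizes,

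pooled RR = [(p_theory + p_non-theory) / 2] / p_pre

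**Model with arm and arm × period added.** The interaction gives

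ratio of RRs = (p_theory / p_pre) / (p_non-theory / p_pre) = p_theory / p_non-theory

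| Post completion, theory / non-theory | Pooled pre-post RR (specified model) | Ratio of RRs (arm × period) |
|---|---|---|
| 60% / 60% | 0.60 / 0.40 = 1.50 | 0.60 / 0.60 = 1.00 |
| 70% / 50% | 0.60 / 0.40 = 1.50 | 0.70 / 0.50 = 1.40 |
| 50% / 70% | 0.60 / 0.40 = 1.50 | 0.50 / 0.70 = 0.71 |
| 80% / 40% | 0.60 / 0.40 = 1.50 | 0.80 / 0.40 = 2.00 |

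Fitting the GEE to these data gave exactly these values. In the last row all the benefit lies in the theory arm, and the specified model still returns 1.50.

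**Simulation of the test.** Assumed: 100–250 resections per network per year (the article's rough estimate), 24 months pre, 9 months post, 50% baseline, and logit-scale standard deviations of 0.5 between networks and 0.2 for network by period. There were 2,000 trials per scenario, with both arms improving equally. The 1.25% level is 5% / 4, taking alpha as 5% and counting one primary and three secondary outcomes.

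| Common improvement | Pre/post test rejects at 5% | at 1.25% | Arm × period test rejects at 5% |
|---|---|---|---|
| RR 1.2 | 88% | 76% | 3.9% |
| RR 1.3 | 99% | 97% | 5.0% |

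The arm × period test used a Kauermann-Carroll variance and t with 6 degrees of freedom. The 88% and 99% are not false-positive rates: completion really did improve, so they are power for a common change. They show that the planned test can be strongly positive when the arms do not differ at all.

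**Precision of the randomised contrast.** Under the same assumptions, a network-level t-test of log pre-post change (4 versus 4) gives:

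| True ratio of RRs | Power at 5% | Power at 1.25% |
|---|---|---|
| 1.2 | about 24% | about 8% |
| 1.5 | about 76% | about 44% |

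Allocation within state allows C(4,2) × C(2,1) × C(2,1) = 6 × 2 × 2 = 24 arrangements. A stratified permutation test therefore cannot give a two-sided p-value below 2/24 = 0.083, so inference on the arm term will depend on the model and its small-sample correction.

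**The case against.** The strongest reply is that this is a condensed article. Its aims commit it to a between-arm comparison, it never says the RR is pooled over arms, and a full analysis plan could fit the model by arm or add a product term. That would carry weight if the article were silent. It is not: it fixes the exposure, its levels, the covariates, the selection rule, the test and the follow-on analysis, and together these specify a different contrast from the one the trial was designed for. What stands is a limit on the wording. The gap is in the analysis as written; the planned data would support the comparison. Separate models by arm would not close it, because comparing two significance results does not test their difference.

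The second reply concerns secular change. Calendar period is a candidate covariate, and if networks start implementing at different dates, adjusting for it could partly separate trend from exposure. That is fair, so the confounding is a matter of degree. But quasi-AIC may drop the term, and keeping it adds no arm contrast.

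The third is that the baseline rate and variance components are assumed. This affects the percentages but not the main result, because no term in the model carries arm.

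**Conclusion.** The concern holds and must be fixed. The only specified model for the clinical outcomes leaves out the randomised contrast. Its coefficient stayed at 1.50 while the true between-arm ratio of RRs ranged from 0.71 to 2.00. The conclusion follows from the model's terms. The constructed data, with a common 40% baseline and equal arm sizes, only illustrate it; the rejection and power percentages do depend on the assumed inputs. The pre-post RR is also not a randomised comparison and remains open to secular change to a degree that depends on whether calendar period stays in the model.

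**What to change.** Fix the primary model in advance as

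log(μ) = state + arm + period + arm × period + prespecified covariates

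with arm, period and their product outside quasi-AIC selection. The primary result is exp(arm × period), the theory pre-post RR divided by the non-theory pre-post RR, with its confidence interval, and the test falls on that term. Arm as a main effect alone is not enough, because the outcome is a change. Report the pre-post RR within each arm as secondary and label it uncontrolled.

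Then bring the other sections into line: define the primary outcome as the between-arm difference in change, apply the small-sample analysis to the arm × period term, reword Phase 7 and the Discussion to match, and aim the deferred power calculation at this term.

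This needs no new data, and Trial status says data collection has not started, so it can be done before outcomes are seen. The price is precision, as the power figures above show. State adds two parameters to a model with eight clusters, and those figures do not include it. The low power belongs to the randomised question with eight networks and is better stated openly than hidden behind a more precise answer to a different question.

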#### Post-implementation outcomes

The primary post-implementation quantitative outcome will be the change in the proportion of patients with risk-appropriate completion of the site-specific LS tumour testing and referral pathway within 2 months of CRC resection. Secondary outcomes will be (1) proportion of high risk-patients who were referred to the FCCs (sensitivity of referral), (2) proportion of referred patients who attended FCC and (3) proportion of patients with missing testing and referral data.

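### The single primary outcome shares one Bonferroni correction with three secondary outcomes, which is valid but inefficient; any return to full alpha has to come with the small-sample correction

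*Protocol article*

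**What the plan says.** Under Post-implementation outcomes, the protocol article declares one primary: "The primary post-implementation quantitative outcome will be the change in the proportion of patients" who complete their site's pathway appropriately for their risk, judged two months after surgery. Three secondaries follow. Two are clinical: how many high-risk patients are referred to a familial cancer clinic, and how many of those referred attend. The third concerns data completeness: "3) proportion of patients with missing testing and referral data".

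Under Assessing clinical practice change, one analysis paragraph covers all of them: "The analysis of each dichotomous study outcome will be conducted at the individual patient level". Every outcome gets its own two-sided test, and the rule for multiplicity is given in a single clause: "with the significance threshold defined using the Bonferroni correction for the number of outcomes tested". No outcome is exempted and no order of testing is set. The base alpha, the number of outcomes and the resulting threshold are not printed.

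The same section specifies GEE with robust standard errors and an exposure defined as pre- or post-implementation status. It acknowledges that few clusters can inflate type I error. It nevertheless keeps the small-sample correction as a supplementary analysis, for outcomes already found robustly significant. The section on sample size and statistical power defers the power calculation until baseline data exist.

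**The concern.** Naming one primary outcome in advance normally lets it be tested at the full significance level, with the secondaries following behind it. Under the stated rule the primary gets no such benefit: it carries the same reduced threshold as each secondary.

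Three features make this a poor bargain.

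- Primary-first testing gives the same family-wise control over all four outcomes without reducing the primary's alpha.
- One member of the family is the proportion with missing data. The analysis section codes missing tests and referrals as not done, so this measure already feeds into the primary outcome, and the primary still gives up alpha for it.
- The primary's threshold depends on how many secondaries end up being tested, and that number is not fixed in the text.

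What is at stake is power for the main question. The trial has eight already-randomised networks, so lost power cannot easily be bought back with more clusters.

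**Working it through.** **Inputs.** From the protocol: one primary plus three secondaries, so m = 4; two-sided tests; eight clusters. Assumed, because the protocol does not state them: family-wise alpha 0.05, and a planned power of 80% or 90% for the primary contrast at 0.05. The plan has no figure of its own to reproduce.

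**Step 1: threshold.** alpha/m = 0.05/4 = 0.0125. If only three outcomes are tested, 0.05/3 = 0.0167.

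**Step 2: does the rule control error?** 4 × 0.0125 = 0.05 at most; if the tests are independent, 1 − (1 − 0.0125)^4 = 0.0491. Given tests that hold their nominal level, the answer is yes.

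**Step 3: power cost on a normal reference.** Power at the reduced level = Φ(z(0.975) + z(power) − z(1 − alpha/2m)). The critical value is 2.498 for m = 4 and 2.394 for m = 3.

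| Power at 0.05 | Standardised effect | m = 4 | m = 3 |
|---|---|---|---|
| 80% | 1.960 + 0.842 = 2.802 | Φ(2.802 − 2.498) = 61.9% | Φ(2.802 − 2.394) = 65.8% |
| 90% | 1.960 + 1.282 = 3.242 | Φ(3.242 − 2.498) = 77.2% | Φ(3.242 − 2.394) = 80.2% |

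Information needed to restore power at m = 4: ((2.498 + 0.842)/2.802)² = 1.42 times for 80%, and ((2.498 + 1.282)/3.242)² = 1.36 times for 90%.

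**Step 4: what few clusters do to the nominal level.** Suppose the robust test statistic behaves as t on 6 df (eight clusters minus two) but is judged against normal critical values:

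- nominal 0.05: 2 × P(t6 > 1.960) = 0.098
- nominal 0.0125: 2 × P(t6 > 2.498) = 0.047

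On 7 df the two values are 0.091 and 0.041. Four outcomes each tested at an actual 0.047 give a family-wise bound of 4 × 0.047 = 0.19, so on this reference the present rule does not hold 5% across the family either.

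**Step 5: net power change on that reference.** The 5% critical value of t on 6 df is 2.447. The uncorrected Bonferroni threshold is 2.498, almost the same. A contrast with 80% power at 2.447 has 78.7% at 2.498, and 90% becomes 89.1%. Moving the primary to a corrected 5% test therefore gains only about one percentage point over the present uncorrected rule.

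**The case against.** The strongest reply is that nothing here is wrong. Bonferroni over every tested outcome is pre-specified and valid, and it lets each secondary be claimed whether or not the primary succeeds. A hierarchy gives that up. This stands: the point concerns efficiency, and a reader who inferred that the correction has no inferential purpose, or that it inflates type I error, would go beyond the text.

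The second reply is that 0.0125 and any power loss are inferred. This also stands. The protocol prints no alpha, count, power, effect size or intra-cluster correlation, and the deferred power calculation could use whatever threshold applies.

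A reader might also infer a far larger loss by taking a between-arm t test on 6 df at both levels. The critical value then rises from 2.447 to 3.521, and 80% power falls to 50%. The protocol does not support that as a description of its main analysis: it specifies robust GEE with a pre/post exposure, names no t reference, and applies small-sample correction only afterwards to significant outcomes.

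The most important reply concerns the remedy. Restoring 0.05 to the primary and changing nothing else could let the actual error rate run near 0.098 (step 4), so one cannot say that family-wise error simply stays at 5%. This is accepted, and it shapes the fix. It does not rescue the present rule as a design choice: the protocol offers Bonferroni only for the number of outcomes, and any offset against small-cluster bias is incidental.

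**Conclusion.** The point holds as one of inefficiency. Read as written, the rule puts the single primary in one Bonferroni family with three secondaries, including a data-completeness measure, when primary-first testing would protect the same four outcomes.

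If the base alpha is two-sided 0.05, all four outcomes are tested and a normal reference applies, the cost is about 18 points from 80% power and 13 points from 90%. With three outcomes it is about 14 and 10 points. These losses are conditional on assumed starting powers and do not describe the trial's actual power, which is unstated.

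If the statistic instead behaves as t on 6 df, the net power gain from changing the rule and adding the correction is about one point, and the gain lies mainly in an error rate that can be defended. On either reference the wording should change, and the unstated base alpha and outcome count should be fixed.

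**What to change.** Replace the multiplicity sentence under Assessing clinical practice change so that it:

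1. states the base alpha, for example two-sided 0.05;
2. tests the primary outcome alone at that level;
3. tests the two clinical secondaries (referral of high-risk patients and clinic attendance among those referred) only if the primary is significant, by Holm or in a fixed order;
4. reports the missing-data proportion descriptively, outside the testing family;
5. requires a primary claim to be significant under the small-sample correction as well, by promoting the planned supplementary analysis to a condition of the claim. The same condition should apply to the secondaries if family-wise control is to hold for them too.

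The cost is a few sentences. According to Trial status, data collection had not commenced, and the deferred power calculation needs a fixed alpha in any case. There are two downsides. Secondaries cannot be claimed if the primary fails. Also, the protocol itself regards small-sample corrections as too conservative with eight clusters, so the choice of correction should be named and the power calculation done under it.
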